#### Maternal STH infection and intensity

Stool specimens will be obtained from women at baseline and at 6 months of follow-up in order to assess the prevalence and intensity of STH infections. In the case that a woman is unable to provide a stool specimen at the time of the visit, a small plastic container labelled with her unique study identification code will be left with her and a research assistant will return the following day for collection. Stool specimens will be transferred to the laboratory where these will be analysed using the Kato-Katz method by a trained microscopist. This technique is recommended for the assessment of STH prevalence and also to quantify the intensity of infection (ie, eggs per gram of stool).^52^

### Substudy

During initial informed consent procedures, women will be asked if they would like to take part in a substudy to assess breast milk quality and quantity. Of those who agree to participate, a random sample of 200 mother-infant pairs will be selected. Breast milk quality and quantity will be assessed in the subsample at 1 and 6 months following delivery. Each time point will consist of six home visits over a 2-week period, on days 1, 2, 4, 5, 14 and 15.

#### Breast milk quality assessments

Quality of breast milk will be assessed by collecting a 50 mL milk sample from mothers. To standardise breast milk collection methods, every effort will be made to collect samples between 8:00 and noon to avoid extremes in diurnal variations.^34^ Women will be assisted in providing a breast milk sample with a hospital-grade electronic breast pump. Collection will occur by pumping milk into a presterilised tube with a leak-proof seal from the breast from which the infant has not fed for 2 h. All milk samples will be transferred to the local laboratory on ice. Macronutrient assessment will be completed on the same day of collection using the MIRIS Human Milk Analyser (HMA, Miris, Uppsala, Sweden). This machine analyzes the macronutrient composition of breast milk, including fat, protein, lactose, energy and dry matter from a 1–3 mL sample in 60 s. The remainder of each sample will be divided into two presterilised tubes and stored at −80°C; these will then be transported on dry ice to Ghent University (Belgium) and to the Western Human Nutrition Research Center (WHNRC) (California) for micronutrient and immunological assessment. Breast milk quality indicators include: IgA, IgG, lactoferrin, lysozymes, vitamins A, B1, B2, B3, B6, B12, C and D, calcium, copper, iron, zinc, free fatty acids, triglycerides and phospholipids. At 1 month following delivery, the breast milk sample will be obtained on day 1 of the 2-week assessment. At 6 months following delivery, the breast milk sample will be obtained on day 15 of the 2-week assessment (figure 3).

**Figure 3 BMJOPEN2015008560F3:**
[figure not shown]
Timeline of data collection for milk quality and quantity in random sub-sample of participants. Each milk assessment is conducted over a 2-week period.

#### Breast milk quantity assessments

Quantity of breast milk transferred from the mother to the infant will be measured using the ‘dose-to-the-mother’ deuterium-oxide turnover technique.^53^
^54^ In addition to optimising feasibility, efficiency and accuracy, this method is the most appropriate because it provides an estimation of water intake from both breast milk and non-breast milk sources.

On day 1, a baseline 3 mL urine sample will be collected from mothers and their infants. Subsequent to urine collection, mothers will receive a preweighed 10 g oral dose of deuterium oxide (99.8% purity), accurate to the nearest 0.001 g. Research assistants will return to participants’ homes to collect four urine samples from mothers on days 2, 5, 14 and 15, and five urine samples from infants on days 2, 4, 5, 14 and 15 (figure 3). Mothers will be asked to provide a urine sample in a small plastic container during the home visit. Infant urine samples will be obtained using paediatric urine bags. Samples will be transferred into 3 mL cryogenic tubes and stored at –20°C. Frozen urine samples will be transported to the Instituto de Nutrición y Tecnología de los Alimentos (INTA) at the University of Chile for laboratory analysis using isotope ratio mass spectrometry.

Infant water intake from breast milk and non-breast milk will be calculated by fitting isotope data to a model for water turnover in mothers and infants, and transfer of milk from mother to infant using assumptions and equations described in previous studies.^53^
^55^
^56^ Breast milk intake and total water intake will be expressed as g/day. This measure will represent the mean grams of breast milk transferred from mother to infant per day during each of the two 14-day assessment periods.

### Statistical analyses

#### Descriptive analyses

Study flow, including participant consent and confirmation, recruitment, eligibility, and losses to follow-up will be depicted in a Consolidated Standards of Reporting Trials (CONSORT) flow diagram. Continuous and categorical variables at baseline will be expressed as means (with SDs) and proportions, as appropriate, for description of the study population and to allow for comparisons in prognostic variables between intervention groups. Primary and secondary analyses will be performed according to the intention-to-treat principle.

#### Primary analysis

The primary outcome, infant weight gain (in grams), will be compared between the two intervention groups using a Student's t test. In addition to estimation of crude intervention effects, multivariable linear regression analysis will be used to compare infant mean weight gain between intervention groups, while adjusting for baseline covariates that were a priori determined to be important confounders in the published literature.^57^ These include maternal age, parity, deworming in the past 6 months, intention to breastfeed, and infant gestational age.^58^ Adjusted analyses will be reported as mean differences and 95% CIs.

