### Outcomes

#### Primary outcome

The primary outcome is infant mean weight gain between birth and 6 months of age. Infant weight gain is thought to be the most accurate measure of breastfeeding adequacy and sufficient milk transfer from mother to breastfeeding infant.^6^ It is also an important indicator of infant growth in the first year of life.^35^
^36^

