#### Anthropometric measurements

Weight will be measured in duplicate at birth, 1, 6, 12 and 24 months using a portable electronic scale, accurate to the nearest 0.01 kg, calibrated daily using standard weights (Seca 354, Seca Corp., Baltimore, USA). Length will be measured in duplicate at birth, 1, 6, 12 and 24 months as recumbent crown-heel length on a flat surface using a measuring mat (Seca 417, Seca Corp., Baltimore, USA), accurate to the nearest millimetre. Both weight and length are measured in the unclothed infant. Head circumference (HC) will be measured in duplicate at birth, 1, 6, 12 and 24 months using a non-stretch Teflon measuring tape (Seca 212, Seca Corp., Baltimore, USA), accurate to the nearest millimetre. Mid-upper arm circumference (MUAC) will be measured in duplicate at 6, 12 and 24 months using a non-stretch measuring tape (UNICEF S0145620), accurate to the nearest millimetre. The mean of the first and second anthropometric measurements will be used in the analyses.

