#### Subgroup analyses

To evaluate the presence of potential effect measure modification due to infant sex, birthweight, and birth length on deworming, interaction terms will be included in separate multivariable linear regression models with the primary outcome, infant mean weight gain. These analyses will examine if there appears to be effect measure modification by sex, birthweight and birth length, and if so, they will estimate the added value of the intervention in potentially vulnerable subgroups. They will also provide insight into whether deworming can improve growth trajectories separately for boys and girls, as well as for infants born with low birthweight and birth length. If effect measure modification is found, results will be reported separately by subgroup.

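### The primary comparison is an unadjusted t test and the supporting regression omits birth weight and infant sex: the plan forgoes a free, probably modest gain in precision

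*Protocol article*

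**What the plan says.** Under Primary outcome, the article states: "The primary outcome is infant mean weight gain between birth and 6 months of age". Under Primary analysis, this outcome "will be compared between the two intervention groups using a Student's t test". A second analysis follows: "In addition to estimation of crude intervention effects, multivariable linear regression analysis will be used to compare infant mean weight gain between intervention groups". Its covariates are chosen by "adjusting for baseline covariates that were a priori determined to be important confounders in the published literature", and the list reads: "These include maternal age, parity, deworming in the past 6 months, intention to breastfeed, and infant gestational age". The Secondary analyses section applies the same set to the secondary outcomes.

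Birth weight and infant sex are not in the list, but other sections show that both are available:

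- Anthropometric measurements: "Weight will be measured in duplicate at birth, 1, 6, 12 and 24 months".
- Secondary analyses: the growth z-scores are computed separately by sex and are referenced to age, so sex and age at measurement must be recorded.
- Subgroup analyses: models of the primary outcome will look for "effect measure modification due to infant sex, birthweight, and birth length". Sex and birth weight thus enter models of weight gain, but only to test interactions.

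**The concern.** In a randomised trial the main reason to adjust is that a covariate predicts the outcome, not that it confounds. Choosing covariates as confounders can miss strong predictors, and that seems to have happened here. The plan builds sex and age into its z-scores, yet it models raw weight gain without sex in either the crude or the adjusted analysis.

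A t test on weight gain fixes the coefficient of birth weight at 1. A regression estimates that coefficient. With 1:1 allocation and about 800 infants, it is asymptotically no less precise.

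Two things are at stake. One is residual variance that could be removed at no cost, in a trial aimed at a difference of about 0.2 SD (0.2/1.01). The other is chance imbalance in birth weight or sex, which stays in both the crude estimate and the planned adjusted estimate.

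**Working it through.** **Inputs from the article.** Sample size section: difference 0.2 kg, SD 1.01 kg (variance 1.0201), two-sided alpha 0.05, power 0.80, loss 20%, total 1010. Randomisation section: 1:1 allocation. No R-squared or correlation is given, so every value below that concerns explained variance is an assumption.

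**1. The plan's own figure.** Per arm, n = 2 × (1.960 + 0.842)² × 1.0201 / 0.2² = 400.3, so 401. Dividing by 0.8 gives 502 per arm, 1004 in total. The exact t calculation gives 402 evaluable and 503 enrolled per arm, 1006 in total. The stated 1010 is reproduced within rounding.

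**2. Power of the planned t test.** Evaluable infants: 1010 × 0.8 = 808, or 404 per arm. SE = 1.01 × √(2/404) = 0.0711 kg. Power = Φ(0.2/0.0711 − 1.96) = 80.4% (exact t: 80.3%). The 95% CI half-width is 1.96 × 0.0711 = 0.139 kg.

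**3. What the added covariates might explain (assumed).**

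- *Infant sex.* With half the infants boys and a boy–girl difference d in gain, R² = (d²/4)/1.0201. For d = 0.2 to 0.5 kg this is 1% to 6%.
- *Birth weight.* The outcome already subtracts birth weight, so only the departure of its slope from 1 counts. Let s₀ be the SD at birth, s₆ the SD at 6 months and r their correlation, with s₆ solved from s₆² + s₀² − 2r·s₀·s₆ = 1.0201. Then R² = (r·s₀·s₆ − s₀²)² / (s₀² × 1.0201). For s₀ = 0.40 to 0.50 kg and r = 0.2 to 0.6 it runs from about 0% to 10%, and it is close to zero at r near 0.4. Example: s₀ = 0.40 and r = 0.6 give s₆ = 1.198 and R² = 10%.
- *Exact age at the 6-month weight (optional).* With visits spread evenly over ±0.5 month and a slope of 0.3 to 0.5 kg/month, R² = (1²/12) × slope² / 1.0201 = 1% to 2%. Over ±1 month it would be 3% to 8%. The article does not state the visit window.

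If the parts are treated as additive, sex and birth weight together give roughly 1% to 16%. Age adds 1% to 2% under the narrower window. A range of 5% to 20% is used below, with 2% shown as a pessimistic case.

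**4. Effect on precision.** Residual SD = 1.01 × √(1 − R²), with 404 per arm and 0.2 kg.

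| Assumed R² | Power | 95% CI half-width (kg) | Narrowing, 1 − √(1 − R²) |
|---|---|---|---|
| 0 | 80.4% | 0.139 | – |
| 0.02 | 81.1% | 0.138 | 1% |
| 0.05 | 82.3% | 0.136 | 3% |
| 0.10 | 84.3% | 0.132 | 5% |
| 0.20 | 88.2% | 0.125 | 11% |

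These gains are measured against the t test. Against the planned regression, only the part that its five covariates do not already explain would count. Gestational age may carry some of the birth-weight information. The article gives no basis for computing that increment.

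**5. Size of a chance imbalance.** The SE of the difference between arms in the proportion of boys is √(0.25 × 2/404) = 0.035. With d = 0.2 to 0.5 kg, a one-SE imbalance moves the crude estimate by 0.035 × 0.2 = 0.007 kg to 0.035 × 0.5 = 0.018 kg. This is small against 0.2 kg, but it is removable.

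**The case against.** The strongest reply is that nothing here is an error. The trial is sized for a two-sided t test and uses one. Under randomisation that test is valid and unbiased, and its stated power is reproduced. A simple pre-specified test supported by an adjusted model is a defensible design. All of this stands, and it limits the point to an improvement.

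Several stronger readings are tempting, but the article does not support them.

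- *The trial loses planned power.* It does not. About 80% is delivered without adjustment.
- *No primary analysis is identified.* The t test comes first under Primary analysis, the regression is introduced as additional, and the sample size rests on the t test. The t test is readable as the lead, although the article promises mean differences and CIs only for the adjusted analyses, and one explicit sentence would help.
- *Adjustment could explain 30% of the variance and lift power to 92%.* Nothing in the article supports that figure. Birth weight may add little to a change score.
- *Visits spread over 5 to 7 months add noise.* That age range describes the 2010 survey used for planning, not this trial's visits. Its spread is already part of the 1.01 kg SD.
- *Exact age at the visit belongs with the baseline covariates.* It is recorded after randomisation and may be used only if visit timing does not depend on arm. Blinding of participants and research assistants supports that assumption.

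It can also be said that the wording introducing the covariates leaves the list open. Its reuse for the secondary outcomes, as the covariates already mentioned, makes it work as a fixed list.

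**Conclusion.** The point holds as a forgone improvement. The omission of birth weight and infant sex is plain in the text, and so is their availability. The direction is also secure: with equal allocation and about 808 evaluable infants, adding baseline predictors cannot asymptotically reduce precision.

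The size is uncertain and probably modest. Under an assumed R² of 5% to 20%, power is about 82% to 88% instead of 80%, and the interval is about 3% to 11% narrower. At the low end of the assumptions the gain is close to nil. The validity of the t test and the adequacy of the sample size are not in question.

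**What to change.** Before unblinding, name one primary analysis: a linear regression of 6-month weight (or weight gain) on arm, birth weight, infant sex and the five covariates already listed. With birth weight in the model, either response gives the same arm coefficient. Report the adjusted mean difference with its 95% CI and p-value as the primary result, and keep the t test as supportive.

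Exact age at the 6-month measurement may be added, with the assumption stated that visit timing does not depend on arm.

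For the z-score outcomes, add the corresponding birth z-score where the measurement was taken at birth. Weight, length and head circumference have a birth value. Mid-upper arm circumference is first measured at 6 months and has none.

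The cost is wording in the statistical section. The sample size, visits and data collection stay as they are, and the calculation based on the t test can stand as conservative.

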#### Secondary analyses

Continuous outcomes will be modelled using multivariable linear regression and dichotomous outcomes will be modelled using multivariable logistic and log-linear regression methods. Log-linear regression will be used instead of logistic regression when the prevalence of the outcome is high (ie, >20%), as it is more appropriate for this situation. Secondary analyses will be adjusted for the baseline covariates mentioned above.

Sex-specific weight-for-age, weight-for-height, height-for-age, MUAC-for-age and HC-for-age z-scores will be calculated using WHO Anthro software (V.3.2.2, 2011) and macros.^59^ Underweight, wasting and stunting will be defined as z-scores for weight-for-age, weight-for-height, height-for-age, respectively of <2 SDs from the median of the WHO reference population, according to the WHO Child Growth Standards.^60^

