#### Secondary outcomes

Secondary infant outcomes include weight and height indices (ie, z-scores for weight-for-age, weight-for-height and height-for-age) and WHO/UNICEF Integrated Management of Childhood Illness (IMCI) indicators of infant morbidity (ie, occurrence of diarrhoea, respiratory illness, fever, and ear infection) in the previous 2 weeks.^37^ Maternal outcomes will include the prevalence and intensity of STH infection (combined and by species), anaemia, self-reported fatigue and breastfeeding practice, and breast milk quality and quantity. All secondary outcomes will be ascertained at 1, 6, 12 and 24 months following delivery.

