### Sample size and power calculations

The sample size is calculated based on the primary outcome, infant mean weight gain between birth and 6 months of age. An estimate of mean weight gain was obtained from data on children aged between 5 and 7 months residing in Belén in 2010. The estimate of 4.24 kg with a SD of 1.01 kg is the weight gain expected in the placebo group. Previous authors have claimed that an infant mean weight gain difference of approximately 500 g is clinically meaningful from trials on enriched formula feeding in infants.^36^
^38^
^39^ However, since the intervention for the proposed trial is given to women rather than infants, and since there is the possibility for effect dilution (ie, treating both STH infected and non-infected mothers), a mean weight gain difference of at least 200 g is expected between the two intervention groups. This difference in infant mean weight gain is also considered to be clinically significant.^40^

The sample size calculation is, therefore, based on an expected effect size of 0.2 kg and a SD of 1.01 kg, a significance level (α) of 0.05 and a power (1-β) of 0.80. As informed by a previous study in the same hospital population,^41^ the final sample size takes into account a 20% loss to follow-up. Based on the above specifications and a two-sided independent t test, we estimate that 1010 participants is the total sample size needed to declare that infant weight gain is different between intervention groups.

This trial will have sufficient power to detect a difference in proportions as low as 4% for moderate/heavy STH intensity (control group: 6% vs experimental group: 2%),^17^ as well as differences in species-specific STH infection (ie, hookworm, *Ascaris*, *Trichuris*) and infant morbidity indicators (ie, recent occurrence of diarrhoea, respiratory illness, fever, and ear infection), since the differences in proportions between intervention groups for these outcomes are expected to be even larger.^17^
^42–44^ The study will also have sufficient power to detect a clinically meaningful mean difference of 0.5 in z-scores for weight-for-age, weight-for-height and height-for-age,^45^ and a difference in maternal haemoglobin levels similar to those observed in other studies on anthelmintic administration.^13^
^17^
^46^ Sample size and power calculations were conducted using PS Power and Sample Size Calculations V.3.0 (Copyright 1997 by Dupont and Plummet).

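### The maternal soil-transmitted helminth (STH) models leave out the baseline stool result, so the 6-month infection comparisons give up precision

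*Protocol article*

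**What the plan says.** - Protocol article, Primary analysis: the weight-gain regression is described as "adjusting for baseline covariates that were a priori determined to be important confounders in the published literature". The list follows: "These include maternal age, parity, deworming in the past 6 months, intention to breastfeed, and infant gestational age".
- Secondary analyses: "Secondary analyses will be adjusted for the baseline covariates mentioned above". The same section gives the models. "Continuous outcomes will be modelled using multivariable linear regression", and dichotomous outcomes by logistic regression, or by log-linear regression when the outcome prevalence exceeds 20%.
- Maternal STH infection and intensity: "Stool specimens will be obtained from women at baseline and at 6 months of follow-up". The Kato-Katz method is used for prevalence and also to "quantify the intensity of infection (ie, eggs per gram of stool".
- Secondary outcomes: prevalence and intensity of maternal STH infection are listed together, overall and by species.
- Sample size and power calculations: intensity appears there as a proportion, moderate/heavy infection in 6% of controls against 2% of treated women.
- Subgroup analyses: the factors are infant sex, birthweight and birth length. Baseline STH status is not used there either.

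**The concern.** The covariates were chosen for infant weight gain. Breastfeeding intention and gestational age have no obvious bearing on whether a mother carries worms six months later, and deworming in the past 6 months is at most an indirect marker of her starting burden. The direct measure, her own baseline stool, is collected, but the adjustment rule passes over it.

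This is a stated rule, not just detail left unsaid: it names what the secondary models adjust for.

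What is at stake is the precision of the result that shows whether the drug lowered worm burden. In the trial's rationale that is the first step towards better maternal and infant health. If weight gain shows no difference, the STH comparison helps to separate a drug that did not reduce worms from a reduction in worms that did not help infants. A tighter estimate serves that purpose and needs no new data.

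**Working it through.** **1. The plan's own figures.** With difference 0.2 kg, SD 1.01 kg, two-sided 5% and 80% power, n per arm = 2 × (1.960 + 0.842)² × 1.01² / 0.2² = 401 after rounding up. Then 802 / 0.80 = 1003, or 1006 with the exact t distribution. The stated 1010 is reproduced. After 20% loss, 1010 × 0.80 / 2 = 404 per arm remain.

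For moderate/heavy intensity at 6% against 2% with 404 per arm, the pooled null SE is √(2 × 0.04 × 0.96 / 404) = 0.01379 and the alternative SE is √((0.06 × 0.94 + 0.02 × 0.98) / 404) = 0.01372. Power = Φ((0.04 − 1.96 × 0.01379) / 0.01372) = 82.8%. The protocol's claim of sufficient power holds without baseline adjustment.

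**2. What adjustment buys in general.** Adding a baseline value with correlation ρ to the outcome multiplies the residual variance by 1 − ρ². A comparison with 80% power then has power Φ(2.802 / √(1 − ρ²) − 1.960). The protocol gives no ρ, so a range is shown.

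| ρ | Variance kept | Power, from 80% |
|---|---|---|
| 0.2 | 0.96 | 81.6% |
| 0.3 | 0.91 | 83.6% |
| 0.5 | 0.75 | 89.9% |
| 0.6 | 0.64 | 93.8% |
| 0.7 | 0.51 | 97.5% |

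**3. Infection yes/no.** Baseline prevalence p is taken from Study design and setting (45% hookworm, 60% *Ascaris*, 80% *Trichuris*, reported in 2004). The 6-month control risks are assumptions: r₁ if infected at baseline, r₀ if not. Then r = p·r₁ + (1 − p)·r₀, φ = (r₁ − r₀) × √(p(1 − p) / (r(1 − r))), and the variance kept is 1 − φ².

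- The (r₁, r₀) pairs 60/20, 70/20 and 80/30 across the three species give φ of 0.32 to 0.50.
- Smallest gain: p = 0.80, 60/20. r = 0.52, φ = 0.4 × √(0.16 / 0.2496) = 0.320, variance kept 0.897, and 1 / 0.897 = 1.11.
- Largest gain: p = 0.45, 70/20. r = 0.425, φ = 0.5 × √(0.2475 / 0.2444) = 0.503, variance kept 0.747, and 1 / 0.747 = 1.34.
- These pairs therefore give 11% to 34% more effective sample size.
- Weaker persistence, 60/30, gives less. At p = 0.45, φ = 0.301 and 1 / 0.909 = 1.10. At p = 0.80, φ = 0.241 and 1 / 0.942 = 1.06.
- Stronger persistence, 80/20, goes beyond the range. At p = 0.45, φ = 0.598 and 1 / 0.642 = 1.56.

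**4. The same question under the planned model.** At these prevalences the outcome exceeds 20%, so the plan uses log-linear regression. This was simulated as a Poisson risk-ratio model with robust errors: 404 per arm, assumed risk ratio 0.85, 1000 runs per cell (Monte Carlo error at most √(0.25 / 1000) = 1.6 points). Power without and with baseline infection:

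| Persistence (r₁/r₀) | p = 45% | p = 60% | p = 80% |
|---|---|---|---|
| Strong (80/20) | 53% to 68% | 66% to 82% | 85% to 91% |
| Moderate (70/25) | 46% to 52% | 61% to 69% | 74% to 79% |
| Weak (60/30) | gain of 0 to 3 points across the three prevalences | | |

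Rejection under no effect stayed at about 5%.

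**5. Only if eggs per gram is analysed as continuous.** Assumptions: 404 per arm, zero-heavy skewed counts, 20% lower intensity plus 10% clearance, latent correlation 0.6, 400 runs per setting.

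| Setting | Raw linear | Raw + baseline | Log | Log + baseline |
|---|---|---|---|---|
| 80% prevalence, dispersion 0.1 | 25% | 26% | 68% | 76% |
| 80% prevalence, dispersion 0.3 | 55% | 65% | 76% | 87% |

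At 45% prevalence and dispersion 0.3, raw and log without baseline were about equal (28% to 31% against 29%). Rejection under no effect was 3% to 8% throughout.

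**The case against.** **Nothing here is invalid.** Leaving a prognostic covariate out of a randomised comparison causes neither bias nor excess false positives, and the 6% against 2% claim stands at 82.8% power. This is correct, and it limits the point to efficiency on a secondary outcome.

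**The list may not be complete, and an analysis plan may add to it.** The covariates are introduced as examples of what is included, and the article is condensed. That leaves room for an addition. But five covariates are named, one sentence applies them to all secondary analyses, and baseline STH appears in neither place. Amending a stated rule is a fair request.

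**The documents give no persistence figure.** This also stands. Calling the baseline stool the best available predictor is plausible but unsupported, and under weak persistence the gain is small.

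Three stronger readings are tempting and should not be drawn:

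- *Egg counts will be analysed by linear regression on the raw scale.* A reader might infer this by joining the eggs-per-gram definition to the rule for continuous outcomes. No section classes intensity as continuous, and the one place that gives it an analysis form makes it a moderate/heavy proportion.
- *Power for infection nearly doubles.* A logistic simulation in which a single propensity drives both visits moves power from 33% to 63%. The plan prescribes log-linear regression at those prevalences, and under that model the gains were smaller.
- *A weak STH analysis undermines every other outcome.* Weight gain, anaemia and morbidity are separate intention-to-treat comparisons. Their validity does not depend on the precision of the STH estimate.

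**Conclusion.** The point holds as one of lost precision. The adjustment rule for secondary analyses omits baseline STH infection and egg count although both are measured, so the 6-month maternal STH models do not use them.

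The loss is about 4% to 49% of residual variance if the baseline-to-6-month correlation lies between 0.2 and 0.7. For infection yes/no, recovering it is worth about 11% to 34% more effective sample size under the moderate to strong persistence assumed, and 6% to 10% (0 to 3 points of power in the simulation) under weak persistence. All of these rest on assumed persistence.

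The model for continuous egg counts is a conditional matter. It arises only if intensity is analysed on that scale in addition to the moderate/heavy class.

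**What to change.** For the maternal STH outcomes, add baseline infection with the same species, or log(baseline epg + 1), to the existing covariates. Keep the log-linear or logistic model already prescribed. Where the logistic model applies, state that the adjusted odds ratio is conditional on the covariates. For moderate/heavy infection, about 0.06 × 404 + 0.02 × 404 = 32 events are expected, so a single baseline term is enough.

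State how women without a baseline stool are kept in the model, by a missing-indicator or by imputation. That missingness arises before treatment, so either is workable.

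State whether intensity is analysed by class only or also as eggs per gram. If also as eggs per gram, use log(epg + 1) or a count model with bootstrap intervals, name the effect measure, and report it beside the moderate/heavy class. Do not rely on robust standard errors for a negative binomial model: in simulation their nominal 95% intervals covered only 0.86 to 0.93. The bootstrap intervals were not themselves tested here.

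The cost is a few lines of analysis text and no new data. The one small downside is the handling of missing baseline stools.

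### The attained infant z-score models adjust for five maternal and pregnancy covariates but not for the infant's own size at birth, which is measured before treatment, so precision and conditional balance are lost

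*Protocol article*

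**What the plan says.** The Secondary outcomes section lists "z-scores for weight-for-age, weight-for-height and height-for-age" and adds: "All secondary outcomes will be ascertained at 1, 6, 12 and 24 months following delivery". The Secondary analyses section also computes z-scores for mid-upper arm circumference (MUAC) and head circumference. No growth index other than the primary outcome is described as a change from birth.

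On modelling, the Secondary analyses section says: "Continuous outcomes will be modelled using multivariable linear regression". It then says: "Secondary analyses will be adjusted for the baseline covariates mentioned above". The list referred to is in the Primary analysis section: "These include maternal age, parity, deworming in the past 6 months, intention to breastfeed, and infant gestational age".

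The Anthropometric measurements section shows that birth values are available: "Length will be measured in duplicate at birth, 1, 6, 12 and 24 months as recumbent crown-heel length" and "Head circumference (HC) will be measured in duplicate at birth, 1, 6, 12 and 24 months". Weight is measured on the same schedule, and MUAC starts only at 6 months. The Interventions and Treatment allocation sections place the tablet after delivery, once the woman has her discharge papers. Birth weight and birth length otherwise appear only in the Subgroup analyses section, as possible effect modifiers of the primary outcome.

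**The concern.** The covariate list was drawn up for weight gain, which already subtracts birth weight. Carried over to attained z-scores, it leaves out the infant's own starting value, usually a leading predictor of later size. Birth size is a true pre-treatment baseline, since a tablet given to the mother after delivery cannot have affected it.

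Leaving it out keeps explainable variation in the residual, so the intervals for the z-score differences are wider than they need be. Any chance difference between arms in birth size, beyond what gestational age accounts for, also stays in the observed comparison. Both effects should be largest at 1 month and fade with age.

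**Working it through.** **The plan's own figure.** Inputs from the sample size section: difference 0.2 kg, SD 1.01 kg, two-sided 5% level, 80% power, 20% loss.

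- n per arm = 2 × (1.960 + 0.842)² × 1.01² / 0.2² = 400.3, so 401.
- 401 / 0.80 = 501.25, so 502 per arm and 1004 in total. The t-distribution version gives 402 per arm and 1006 in total.
- The stated 1010 is reproduced closely. It leaves 1010 × 0.80 / 2 = 404 evaluable infants per arm, used below.

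**Precision without birth size** (z-score SD of 1 assumed; the document gives none).

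- SE of the arm difference = √(2/404) = 0.070, and the 95% half-width is 1.96 × 0.0704 = 0.138.
- Detectable difference at 80% power = 2.802 × 0.0704 = 0.197 z.
- Power for the stated 0.5 z exceeds 99.9%, with SD 1.0 or 1.3. Power for 0.2 z is 81%.

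**Gain from adding birth z, with gestational age already in the model.** Let r1 be the correlation of birth z with follow-up z, r2 that of gestational age with follow-up z, and r12 = 0.5 that of gestational age with birth z. All three are assumptions.

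- R² with both = (r1² + r2² − 2·r1·r2·r12) / (1 − r12²)
- R² with gestational age only = r2²
- Residual variance ratio = (1 − R² both) / (1 − r2²)
- Interval narrowing = 1 − √ratio

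| Visit | r1 | r2 | R² both | Ratio | Variance falls by | Interval narrows by |
|---|---|---|---|---|---|---|
| 1 month, low | 0.60 | 0.30 | 0.360 | 0.640/0.910 = 0.70 | 30% | 16% |
| 1 month, high | 0.70 | 0.35 | 0.490 | 0.510/0.878 = 0.58 | 42% | 24% |
| 6 months, low | 0.40 | 0.20 | 0.160 | 0.840/0.960 = 0.875 | 12.5% | 6% |
| 6 months, high | 0.50 | 0.25 | 0.250 | 0.750/0.938 = 0.80 | 20% | 11% |
| 12–24 months, low | 0.30 | 0.15 | 0.090 | 0.910/0.978 = 0.93 | 7% | 4% |
| 12–24 months, high | 0.35 | 0.15 | 0.123 | 0.877/0.978 = 0.90 | 10% | 5% |

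The gain in equivalent sample size is 1/ratio − 1: about 42–72%, 14–25% and 7–12% more infants at the three stages.

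**Sensitivity.** In nearly every row r2 = r1 × r12, meaning gestational age acts on later size only through birth size. That favours the birth term. If gestational age also predicts 1-month size directly, say r2 = 0.5 with r1 = 0.6, then R² both = (0.36 + 0.25 − 0.30)/0.75 = 0.413. The ratio is 0.587/0.75 = 0.78, a fall of 22%, equivalent to 28% more infants.

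**Carry-over of a chance imbalance at 1 month.**

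- The 95% limit for the arm difference in birth z is 1.96 × 0.0704 = ±0.138.
- With gestational age in the model, the part that remains is 0.138 × √(1 − 0.25) = ±0.12.
- The slope on birth z given gestational age is (r1 − r2·r12)/(1 − r12²): (0.60 − 0.15)/0.75 = 0.6, or (0.70 − 0.175)/0.75 = 0.7.
- Carry-over is 0.12 × 0.6 to 0.12 × 0.7, about ±0.07 to 0.08 z.

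**The case against.** The strongest reply is that this is an efficiency choice and not an error. Allocation is randomised 1:1, so the models are unbiased without birth size. Their standard errors already include the chance variation in birth size, so the 5% error rate and 95% coverage hold. A reader might infer that chance imbalance biases or invalidates the z-score comparisons; the documents do not support that. The imbalance matters only conditionally, for the one allocation that occurs.

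A reader might also infer that the trial is underpowered for its z-score outcomes. It is not: the only target stated is 0.5 z, and the 1-month carry-over, itself an extreme case, is under one fifth of it. The extra precision matters for smaller effects. The primary outcome is planned around 0.2/1.01, about 0.2 SD, because of dilution from treating uninfected mothers. If z-score effects were of that order (an assumption), unadjusted power would be about 81%. A 25% fall in residual variance would raise it to about 91%.

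Three further objections stand in part. Gestational age already absorbs some birth-size variation; the calculation allows for this, and the sensitivity case shows a smaller gain. The gain at 12–24 months is small. The wording that introduces the covariates could be read as an open list, but no birth measure is named in it.

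Finally, it is tempting to extend the figures to underweight, wasting and stunting. They do not carry over. In logistic regression, adding a strong covariate changes the conditional odds ratio being estimated and does not narrow the interval as it does in a linear model.

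**Conclusion.** The point holds as a loss of precision and conditional balance in the linear z-score models, not as a defect of validity or a threat to the stated 0.5 z target. Residual variance would fall by about 30–42% at 1 month, 12–20% at 6 months and 7–10% at 12–24 months, or about 22% at 1 month if gestational age has a direct effect on follow-up size. The 1-month carry-over at the 95% limit of imbalance is about ±0.07 to 0.08 z.

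These sizes rest on assumed correlations, a z-score SD of 1 and 404 infants per arm at every visit. The document supplies none of the correlations and no z-score SD. The direction of the gain does not depend on the exact values, provided birth size predicts later size beyond the listed covariates. The change is worth making because the data are already collected and the gain is appreciable at the earlier visits.

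**What to change.** In the Secondary analyses section, add one sentence, fixed before unblinding: each linear z-score model at each visit includes, besides the five listed covariates, the infant's own birth value of the same index.

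- Weight-for-age: birth weight-for-age z-score.
- Height-for-age: birth length-for-age z-score.
- Head circumference-for-age: birth head circumference z-score.
- Weight-for-height: birth weight and birth length z-scores.
- MUAC-for-age, which has no birth value: birth weight z-score.

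The change is not required in the logistic models for underweight, wasting and stunting.

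No participants, visits or measurements are added. The small cost is a stated rule for the few infants without a birth measurement, for example simple baseline imputation. Fixing the terms in advance also avoids a post hoc choice should birth size prove unequal in the baseline table.
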